The viral load set point (mean of the last two viral load determinations before ART resumption or at study end at week 52) varied between subjects with evidence of favorable effects of Vacc-4x immunization over placebo. In the subgroup of “completer” subjects who remained off ART until Week 52, the median viral load set point was significantly lower ( $p = 0.0397$ ) in the Vacc-4x-treated subjects (22300 copies/ml,  $n = 56$ ) compared to placebo-treated subjects (61900 copies/ml,  $n = 25$ ). In the subgroup of “LOCF” (last observation carried forward), including all subjects off ART until at least Week 40, the median viral load set point was lower in the Vacc-4x group (26775

copies/ml, n = 72) compared to the placebo group (57975 copies/ml, n = 32), but this difference did not reach the level of statistical significance (p = 0.1489).

No safety concern was raised during this study. The study was supervised by a Data Safety Monitoring Board (DSMB).

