## **2.2 Study Endpoints**

### **2.2.1 Efficacy Endpoints**

#### **2.2.1.1 Primary Efficacy Endpoints**

- Viral load set point (mean of VL count Visit 8 and Visit 9) for subjects discontinuing ART according to protocol and *not* resuming ART until Visit 9 compared to:
  - viral load set point\* for subjects not resuming ART before week 52 or later in the CT-BI Vacc-4x 2007/1 study and who entered this study,or if week 52 not reached in the previous study
  - viral load set point\*\* for subjects resuming ART at the earliest week 40 in the CT-BI Vacc-4x 2007/1 study and who entered this study.

*\* The VL set point was defined as the mean of VL count week 48 and week 52 week in subjects who did not resume ART.*

*\*\*The VL set point was defined as the week 40 VL count for subject resuming ART week 40 or the mean of the last two VL counts prior to ART resumption for subjects resuming ART week 44 or later but before week 52.*

Comparison will also be made to pre-ART viral load values, if available from the CT-BI Vacc-4x 2007/1 study.

- T-cell response will be measured by ELISPOT as well as by T-cell proliferative response assay (Flow Cytometry) and intracellular cytokine staining at Visit 2 (before re-boosting), Visit 4 (two weeks after re-boosting), Visit 6, Visit 9 and Visit 10. These will be compared to the responses reported in the study CT-BI Vacc-4x 2007/1.

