**Table 1. Time and Events Schedule**

| Parameters                                                | Screening/
Verification
Inclusion | Re-vaccination cycle |                |      |                     |                           |       |       |                       | Follow-up       |
|-----------------------------------------------------------|-----------------------------------------|----------------------|----------------|------|---------------------|---------------------------|-------|-------|-----------------------|-----------------|
|                                                           |                                         | Re-boost period      |                |      | Follow-up
on ART | ART-free follow-up period |       |       |                       | END of
STUDY |
| Visit:                                                    | 1                                       | 2                    | 3              | 4    | 5                   | 6                         | 7     | 8     | 9                     | 10              |
| Day                                                       |                                         | 1                    | 15±2           | 28±2 | 84±3                | 112±7                     | 140±7 | 168±7 | 196±7                 | 252±7           |
| Week                                                      | -4                                      | 0                    | 2              | 4    | 12                  | 16                        | 20    | 24    | 28                    | 36              |
| Re-boost: Adjuvant + Vacc-4x                              |                                         | x                    | x              |      |                     |                           |       |       |                       |                 |
| DTH a                                          |                                         | x                    |                | x    |                     |                           |       |       |                       |                 |
| ART status                                                | On or Off                               |                      |                |      | Stop g   |                           |       |       | Re-start h |                 |

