## **4 SELECTION AND WITHDRAWAL OF SUBJECTS**

### **4.1 Inclusion**

All subjects to be included will have participated in the CT-BI Vacc-4x 2007/1 study (EudraCT Number 2007-006302-13), completed the immunization regimen with active Vacc-4x and stopped ART at Week 28.

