### **6.3.2.4 Visit 5**

This visit should be 84 ( $\pm 3$ ) days from Visit 2.

If on ART, the subject will be instructed to now stop ART if their CD4 count is  $\geq 350 \times 10^6/\text{L}$  and virally controlled (undetectable VL [ $<50$ copies] over a period of three months on a stable antiretroviral regimen with no more than one blip allowed). If the CD4 count is  $<350 \times 10^6/\text{L}$  and/or the virus is not controlled, the subject will be instructed to remain on ART. The instruction will be based on the results of CD4 count and viral load from this visit. As soon as possible when these

results are available, and at the latest within one week after this visit, the investigator will contact the subject by phone and tell the subject to stop ART, or not to stop ART. Stopping of ART will be done according to local guidelines and their current clinical judgment and based on the individual ART the subjects are receiving. Subjects will be instructed to write down the date(s) when stopping ART and take this information to the investigator at the next visit.

The Investigator needs to see the results from the blood sampling at Visit 5 before the subject can stop ART. The information to the subject that he/she can stop ART and instructions on how to do this can be made by telephone. It is important that the treatment interruption period has a full 16 week duration.

The following procedures will be performed:

- Review of concomitant medications and AEs.
- Physical examination including weight.
- Vital signs (blood pressure, heart rate).
- Clinical chemistry and hematology.
- Viral load, CD4 and CD8 counts.

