### **10.3 Populations to be Analyzed**

The following populations will be used in the analyses:

**Safety:** All subjects who receive at least one re-boosting immunization will be included within the safety population. All safety analyses will be conducted on the safety population.

**Intention to treat (ITT):** All subjects who receive at least one re-boosting immunization and have any post-baseline efficacy data will be included in the ITT population. Unless otherwise indicated, all efficacy analyses will be conducted on the ITT Population.

**Per protocol (PP):** All ITT subjects who receive two re-boosting immunizations, discontinue ART at Visit 5 (as planned) and who do not incur a major protocol violation that would challenge the validity of their data will be included within the PP population. All efficacy analyses will also be conducted on the PP population.

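### The re-boost set-point requires 16 ART-free weeks with no fallback, its comparator only 12 weeks with one, so selection is stricter on the new side of the primary paired test

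*Protocol*

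**What the plan says.** Protocol Section 2.2.1.1 (and the synopsis) takes the re-boost set-point as the mean of the Visit 8 and Visit 9 viral loads, "for subjects discontinuing ART according to protocol and *not* resuming ART until Visit 9". It gives no value to a subject who resumes sooner.

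The comparator from the initial study is the mean of weeks 48 and 52 for subjects still off ART. It also includes a set-point "for subjects resuming ART at the earliest week 40 in the CT-BI Vacc-4x 2007/1 study and who entered this study". For these resumers the value is "the week 40 VL count for subject resuming ART week 40 or the mean of the last two VL counts prior to ART resumption".

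Section 10.6.2.1 makes the comparison of these two values the primary analysis, by Wilcoxon signed rank test. Section 10.3 states: "Unless otherwise indicated, all efficacy analyses will be conducted on the ITT Population". The PP set further requires two immunizations, stopping ART at Visit 5 and no major violation.

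Section 4.4.1.3 lists the grounds for resuming ART. One is a confirmed viral load above 300,000 copies/mL; the others are CD4 and clinical grounds.

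For CD4 and CD8, Section 2.2.1.2 does use the last value before ART is resumed when that happens before Visit 9. The primary endpoint has no such provision.

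**The concern.** Whether a subject has a primary endpoint is decided after treatment, and partly by the variable being measured. A subject whose viral load is very high at Visit 8 can have it confirmed within two weeks and resume before Visit 9, which is four weeks later. The Visit 8 value has been measured but is not used. In the initial study the corresponding week 40 value would have counted.

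When high values are filtered more strictly on one side of a paired difference than on the other, the remaining pairs lean towards a reduction even if re-boosting does nothing. The study is open and single-arm, with 30 to 40 subjects expected, so no control group would reveal such a shift. The ITT label also suggests a broader analysis than the endpoint definition allows.

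**Working it through.** **1. ART-free time required on each side**

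In the initial study the subjects "completed the immunization regimen with active Vacc-4x and stopped ART at Week 28". In this study ART stops at Visit 5 (day 84), and Visits 7 to 9 fall on days "140±7 | 168±7 | 196±7". Section 6.3.2.4 adds: "It is important that the treatment interruption period has a full 16 week duration".

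| Point | Calculation | Nominal ART-free weeks |
|---|---|---|
| Initial study, week 40 | 40 − 28 | 12 |
| Initial study, week 44 | 44 − 28 | 16 |
| Initial study, weeks 48 and 52 | 48 − 28; 52 − 28 | 20; 24 |
| This study, Visit 8 | (168 − 84)/7 | 12 |
| This study, Visit 9 | (196 − 84)/7 | 16 |

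These are nominal times. Visit windows are ±7 days, and the instruction to stop ART can follow Visit 5 by up to a week.

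**2. Who is treated differently**

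| ART resumed after | Old side | New side |
|---|---|---|
| under 12 weeks | no value | no value |
| 12 to under 16 weeks | week 40 or last values before resumption | no value |
| 16 weeks or more | value | value |

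Only the middle row differs. A missing value on either side removes the pair.

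**3. ITT against PP**

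Both sets meet the same endpoint definition, so resumers before Visit 9 are absent from both. Agreement between ITT and PP results would say nothing about this exclusion.

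**4. Possible size**

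The protocol gives no SD, effect size or resumption rate for this comparison, so it offers no figure to reproduce. Section 10.1 counts 88 subjects who completed active immunization and stopped ART. Section 1.4 counts 72 Vacc-4x subjects off ART to at least week 40 and 56 to week 52. With 88 as denominator (an assumption):

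- without a set-point under a 12-week floor: (88 − 72)/88 = 16/88 = 18%
- without one under a 24-week floor: (88 − 56)/88 = 32/88 = 36%

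If the second interruption resembles the first, a 16-week floor loses a share between these two.

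The paired test was simulated with no re-boost effect: 35 subjects, 2,000 runs per setting, and 18% dropped on the old side. Assumed inputs were SD 0.8 log10, within-subject correlation 0.5 or 0.7, and correlation of resumption with viral load 0.5 or 1.0.

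| Dropped on new side | Mean change (log10) | Two-sided rejection at 0.05 | Pairs left |
|---|---|---|---|
| 18% (same rule) | about 0.00 | 4.6% to 5.1% | 24 to 26 |
| 28% | −0.02 to −0.07 | 4.6% to 7.3% | 21 to 23 |
| 36% | −0.04 to −0.13 | 5.3% to 13.5% | 19 to 21 |

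The simulation error near 5% is about √(0.05 × 0.95/2000) = 0.5 percentage points, so the lowest rates cannot be told from 5%. A milder assumed case (SD 0.7 log10, 7% resuming, resumers 0.36 log10 higher, no floor on the old side) gave about 0.01 log10.

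**The case against.** A reader might infer that re-boost failures are removed from the new side only. The documents do not support that. The comparator has its own floor at week 40, which removes early failures of the first interruption, and because the test is paired those pairs go too. Ignoring that floor overstates the effect: dropping 18% to 36% on the new side and none on the old gives −0.04 to −0.24 log10 under the same assumptions. The difference is confined to a four-week window, and the protocol does not say how many subjects would fall in it.

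A reader might also infer from Section 1.4 that this same choice changed the initial study's conclusion. There, completers gave p = 0.0397, whereas with resumers from week 40 included "this difference did not reach the level of statistical significance (p = 0.1489"). Those are Vacc-4x against placebo results, not paired ones. They contrast 24 with at least 12 ART-free weeks, and both arms changed. The medians also moved in opposite directions. In Vacc-4x the ratio is 26,775/22,300 = 1.20 (+0.08 log10); in placebo it is 57,975/61,900 = 0.94 (−0.03 log10). A viral load gap between resumers and completers cannot be taken from one arm alone. What stands is that set-point summaries are sensitive to including resumers.

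Two further points are fair. Several restart grounds are not viral load, which weakens the link with the endpoint. Section 10.5.2 leaves subgroup analyses by ART timing to the SAP, so a sensitivity analysis may already be planned. Neither point changes the primary definition, which the protocol itself fixes.

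**Conclusion.** The concern holds in this limited form. The two sides of the primary comparison use different minimum ART-free times (16 and 12 weeks), and only the old side has a fallback. Subjects resuming in between are dropped as whole pairs, which tends to favour the re-boost because resumption is partly driven by viral load. The ITT primary analysis is in effect restricted to subjects who stayed off ART, and PP does not test that restriction.

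The rules and the week arithmetic come from the protocol. The size does not: about 0.01 to 0.13 log10 rests on assumed SD, correlations and resumption shares, and at the low end it is negligible. The direction is a tendency arising from this asymmetry alone. The net bias of the whole comparison is not established, because the timing of measurement also differs between the two studies. The change is worth making because it is cheap and decides who enters the primary test, not because a large bias has been shown.

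**What to change.** Apply the comparator's rule to both sides in Section 2.2.1.1 and the synopsis:

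- Still off ART at Visit 9: mean of the Visit 8 and Visit 9 viral loads.
- ART resumed at Visit 8, or after it but before Visit 9: the Visit 8 value taken before resumption.
- Pre-stated sensitivity analysis: add subjects who stopped ART at Visit 5 and resumed before Visit 8, using their last off-ART viral load or the worst rank.
- Supportive completer analysis: the present set, not resuming until Visit 9.

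No new sampling is needed, since viral load is taken at every visit. The costs are that some subjects contribute one measurement instead of two and that the result may look less favourable. The change also leaves one difference in place: the new value is read at 12 and 16 ART-free weeks, while that of initial-study completers is read at 20 and 24. The protocol should acknowledge this as a limitation.

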#### **2.2.1.2 Secondary Efficacy Endpoints**

- CD4 counts at all visits in the study, absolute numbers of CD4 counts, and treatment emergent changes of CD4 counts from mean of Screening and Visit 2.
- Change (and percent change) in CD4 count from Visit 5 (discontinue ART) to Visits 6, 7, 8, 9 and 10 (End of Study).
- CD8 counts at all visits in the study, absolute numbers of CD8 counts, and treatment emergent changes of CD8 from mean of Screening and Visit 2.
- Change (and percent change) in CD8 count from Visit 5 (discontinue ART) to Visits 6, 7, 8, 9 and 10 (End of Study).

For each individual subject both the absolute and relative changes in CD4 and CD8 values registered at Visit 5, and at Visit 9 (or the last value before reinitiated ART, if ART reinitiated before Visit 9) will be compared with the corresponding values registered at Week 28 (ART discontinued) and Week 52 (or last visit before ART re-initiation) in the initial study CT-BI Vacc-4x 2007/1 (EudraCT Number 2007-006302-13).

- DTH (both induration and erythema) at Visit 2 and Visit 4, in terms of observed areas ( $\text{mm}^2$  length x height) and also in terms of a positive test, defined as an area  $\geq 10\text{mm}^2$  DTH-tests, both areas and number of positive tests registered at Visit 2 will be compared with the corresponding values registered at Visit 4.

In addition the values for these DTH parameters at Visit 4 will be compared with the DTH response reported at Week 18 in the initial study CT-BI Vacc-4x 2007/1 (EudraCT Number 2007-006302-13).

### **2.2.2 Safety Endpoints**

- Proportion of subjects who experience similar virologic suppression 8 weeks after re-initiation of ART (Visit 10) as before ART interruption (Visit 5 value).
- AEs, recorded continuously from screening to Visit 10 (End of Study).
- Vital signs (heart rate, blood pressure) at Screening, and selected visits through Visit 10 (End of Study).
- Clinical laboratory evaluations (clinical chemistry, hematology) at screening, and selected visits through Visit 10 (End of Study); absolute values and treatment emergent changes from mean Screening and Week 1.

## **3 STUDY DESIGN**

### **3.1 Overall Study Design and Flow Chart**

The study is an open label, multicenter, follow-up, re-boosting study of subjects who previously completed the immunization regimen with Vacc-4x active and stopped ART (at Week 28) in the CT-BI Vacc-4x 2007/1 Study (EudraCT Number 2007-006302-13). No restart of ART is required. The subjects will be re-boosted with two immunizations (Visit 2 and Visit 3) of Vacc-4x, 1.2 mg peptides (12 mg/mL), with a 2 week interval between immunizations.

At Visit 5 ART medication (if being used) will be stopped in subjects whose CD4 count  $\geq 350 \times 10^6/\text{L}$ , for a 16 week period. At Week 29 ART will be restarted, according to the Investigator and subject's decision, and the subjects will be followed for an additional 8 weeks (End of Study; Visit 10).

DTH will be measured at Visit 2, and at Visit 4 (3 weeks after the second re-boosting immunization).

Viral load, CD4 and CD8 counts will be measured at all study visits. T-cell responses will be measured at Visits 2, 4, 6, 9 and 10 (End of Study) both by ELISPOT, T-cell proliferation assay and intracellular cytokine staining.

Vital signs and clinical laboratory tests will be done at all study visits.

Monitoring of AEs and concomitant medications will be done continuously from the time of signing ICF through the End of Study.

**Table 1. Time and Events Schedule**

| Parameters                                                | Screening/
Verification
Inclusion | Re-vaccination cycle |                |      |                     |                           |       |       |                       | Follow-up       |
|-----------------------------------------------------------|-----------------------------------------|----------------------|----------------|------|---------------------|---------------------------|-------|-------|-----------------------|-----------------|
|                                                           |                                         | Re-boost period      |                |      | Follow-up
on ART | ART-free follow-up period |       |       |                       | END of
STUDY |
| Visit:                                                    | 1                                       | 2                    | 3              | 4    | 5                   | 6                         | 7     | 8     | 9                     | 10              |
| Day                                                       |                                         | 1                    | 15±2           | 28±2 | 84±3                | 112±7                     | 140±7 | 168±7 | 196±7                 | 252±7           |
| Week                                                      | -4                                      | 0                    | 2              | 4    | 12                  | 16                        | 20    | 24    | 28                    | 36              |
| Re-boost: Adjuvant + Vacc-4x                              |                                         | x                    | x              |      |                     |                           |       |       |                       |                 |
| DTH a                                          |                                         | x                    |                | x    |                     |                           |       |       |                       |                 |
| ART status                                                | On or Off                               |                      |                |      | Stop g   |                           |       |       | Re-start h |                 |
| Informed Consent                                          | x                                       |                      |                |      |                     |                           |       |       |                       |                 |
| Inclusion/exclusion                                       | x                                       |                      |                |      |                     |                           |       |       |                       |                 |
| Physical examination incl. Weight and Height b | x                                       | x                    |                |      | x                   |                           |       |       | x                     | x               |
| Medical History                                           | x                                       |                      |                |      |                     |                           |       |       |                       |                 |
| Vital Signs                                               | x                                       | x                    | x              | x    | x                   | x                         | x     | x     | x                     | x               |
| Clinical Chemistry/Hematology c                | x                                       | x i       | x i | x    | x                   | x                         | x     | x     | x                     | x               |
| Viral load/CD4 and CD8 Count d                 | x                                       | x i       | x i | x    | x                   | x                         | x     | x     | x                     | x               |
| T-cell Response e /Proviral DNA                |                                         | x i       |                | x    |                     | x                         |       |       | x                     | x               |
| Pregnancy Test f                               |                                         | x                    | x              |      |                     |                           |       |       |                       |                 |
| Adverse Events                                            | x                                       | x                    | x              | x    | x                   | x                         | x     | x     | x                     | x               |
| Concomitant Medications                                   | x                                       | x                    | x              | x    | x                   | x                         | x     | x     | x                     | x               |

a. Immunization for the DTH skin reaction is performed on day indicated; the test is evaluated 48 hours after immunization. This evaluation can be made by the subject, if properly trained.

b. Height only once at Screening.

c. Includes measurements of hemoglobin, CRP, WBC, platelets, creatinine, AST (SGOT), ALT (SGPT), LDH, ALP, γ-GT, albumin, total bilirubin, and β2-microglobulin.

d. Viral load will be quantified by HIV RNA copies/mL using PCR. CD4 and CD8 counts will be determined using flow cytometry.

e. T-cell response will be measured by ELISPOT as well as T-cell proliferative response assay and intracellular cytokine staining.

f. A urine pregnancy test will be administered and a negative test will be confirmed, prior to study drug administration.

g. If on ART subjects whose CD4 count is  $\geq 350 \times 10^6/L$  and virally controlled at Visit 5 are expected to stop ART.

h. Restart according to Investigator's/subject's decision.

i. Blood samples should be taken before immunization (re-boosting).

